## Abstract

**Background:**

The objective of the Balearic Islands Palliative Care (PC) Program is to improve the quality of PC through a shared model consisting of primary health care professionals, home-based PC teams, and PC units in hospitals. According to the World Health Organization (WHO), patients with advanced cancer and other terminal diseases benefit from early identification and proactive PC. We will evaluate the effectiveness of an intervention in which a PC leader is established in the primary health care center, and assess the effect of this intervention on the early identification of patients in need of PC, the efficient use of health care services, and direct health care costs.

**Methods:**

Design: A two-arm cluster randomized clinical trial of 30 Primary Health Care Centers (PHCC) in Mallorca (Spain), in which each center was randomized to an intervention arm or a usual care arm. We expect that the number of patients identified as suitable for PC (including non-oncological PC) is at least 5% greater in the intervention arm.

Sample size: A total of 4640 deceased patients. Outcomes will be assessed by a blinded external review of the electronic records.

Interventions: General practitioners (GPs) and nurse leaders in PC for each PHCC will be appointed. These leaders will help promote PC training of colleagues, improve symptom management and psychological support of patients, and evaluate the complexity of individual cases so that these cases receive assistance from PC home-based teams.

Measurements: Early identification (>90 days before death), evaluation of case complexity, level of case complexity (with referral to a home-based PC team), use and cost of hospital and primary care services, and quality of life during the last month of life (≥2 emergency room visits, ≥2 hospital admissions, ≥14 days of hospitalization).

**Discusion:**

PC leaders in primary care teams will improve the early identification of patients eligible for PC. This initiative could improve the quality of end-of-life care and utilization of hospital resources.

**Trial registration:**

ISRCTN Registry identifier: ISRCTN92479122. Retrospectively registered on 28 February 2017.

## Background

The populations of European countries are getting older, and this is leading to major increases in the number of patients needing palliative care (PC) because of chronic incurable diseases or advanced stages of terminal diseases [1]. The 2013 European Atlas of Palliative Care (EAPC) reported that the use of PC in Europe has increased, although there are variations among countries [2]. Spain, like other European countries, also has an aging population, and thus has initiated an ambitious strategy for PC [3]. There has been wide-spread development of multidisciplinary PC teams in hospitals and primary health care facilities in Spain, and there are currently 284 specific resources for PC, 8 of them in the Balearic Islands [4].

PC was initially proposed for cancer patients [5], but was later extended, although insufficiently, to patients in the later stages of other terminal diseases who had similar needs [6, 7]. Rosenwax [8, 9] classified 9 major causes of death, and this should be considered a minimum required to calculate the needs for PC. Some previous studies explain the development of different illnesses and the care needed during each stage [10–12]. There are models of 3 general groups of patients with chronic progressive illnesses: cancer, organ failure, and dementia/fragility in the elderly. The cancer model is characterized by a short and evident decline, following a variable period of illness with a reasonably predictable decline in physical health. Although cancer can last for many years, the loss of functionality usually only lasts for several months. The organ failure model is characterized by a long period of functional limitations, which can last for about two to five years, in which acute and aggravating episodes occur. Patients usually recover from these acute episodes, although there is an increased loss of functionality. When patients die following an episode, death is typically sudden. The third model of dementia/fragility in the elderly is characterized by a long period of functional decline, with a phase of very low physical and cognitive function that can last for several years. In this model, the decline is progressive and irreversible. Death occurs when the patient is completely dependent on intensive medical care. There are difficulties in identifying the need for PC in these different situations due to differences in the natural courses of the illnesses and the rate of functional status decline.

Initially, caregivers only proposed PC when active treatment could not be prolonged, although it is has long been established that PC must start when active treatment is on-going [13]. There is a general agreement that patients suitable for PC should be identified as soon as possible. The World Health Organization (WHO) emphasized early identification in its definition of PC since 2002: “an approach that improves the quality of life of patients and their families facing the problems associated with life-threatening illness, through the prevention and relief of suffering by means of *early identification* and impeccable assessment and treatment of pain and other problems, physical, psychosocial and spiritual” [14]. Subsequent studies reported that early PC can even prolong survival in patients with some tumors [15, 16]. Thus, the early identification of patients eligible for PC has many benefits, in that aggressive diagnostic and therapeutic interventions are avoided, and unnecessary suffering and costs are reduced [17, 18].

It is important to determine how often PC is needed and the service requirements to calculate the necessary resources. Up to 75% of patient deaths in Spain are due to chronic illnesses from advanced identifiable processes [7]. Murtagh et al. [10] estimated that 63% of deaths were eligible for PC. It is also necessary to determine the incidences of advanced stages of the different pathologies, and this can be estimated from mortality rates. It is also essential to establish the suitable timing for administration of PC [19]. This timing is difficult to predict [20], but an approximation will allow calculation of the prevalence of the problem, planning of services, and estimation of program coverage [21].

The prevalence of cases needing PC will increase with the incidence of the chronic illnesses, the number of eligible pathologies, and the development of PC services. Thus, the need for PC will continue to grow over time. It is therefore essential to identify patients who can only be cared for by conventional services in a primary care or hospital setting, and patients who need specific PC resources (home- or hospital-based), exclusively or in combination with conventional services. The sustainability of the PC model must be based on a shared care model, in which there are general or conventional care services and specialized PC resources [22].

Previous studies assessed the effectiveness of home-based PC in cancer patients [23], but there are fewer studies of PC for patients with chronic but non-oncologic diseases [24]. In Spain, at least at the primary care level, the Spanish Society of Family and Community Medicine and the Spanish Society of Palliative Care reached a consensus regarding their roles in home-based care, and have a long-established commitment to PC [25].

A complex case needing PC [26, 27] is a case with advanced-stage cancer or a terminal illness that is difficult to manage, so that special interventions are needed. Early and accurate identification of patients who require PC would help to identify the need for different PC resources, so that the best response can be provided according to the disease progression and the changing needs of patients. On the other hand, at least in patients with advanced cancer who have a mean survival time of 99 days, three-quarters of this period is spent at home, making the role of the primary care doctor and nurse essential. There are multidisciplinary PC home-based teams, but they should only be required when the complexity of care requires their intervention [21].

In Spain, primary health care doctors, nurses, and other support staff (psychologists, social workers, and others) work in primary health care centers, which care for a mean of 20,000 patient registered. Each doctor and nurse has a mean of 1700 patients registered. The general practitioners (GPs) and community nurses have diverse responsibilities, and must acquire and maintain multiple professional skills so they can appropriately care for patients with diverse health problems. Although each professional cares for assigned patients, there are shared responsibilities within a team, determined by the skills of the health care provider and the medical problem of the patient. PC is a field in which the presence of a leader or expert in each team is considered beneficial, as proposed in the Andalusian and Ballearic Palliative Care Plan [27, 28].

The aim of this randomized clinical trial (RCT) is to assess the effect of the appointment of a PC leader or expert to each health care team who can provide early identification of patients needing PC, encourage the appropriate use of health care services according to the complexity of the case, better satisfy the needs of patients with terminal illnesses, and reduce direct health care costs.

## Methods

### Design

The study is a multicenter two-armed cluster randomized clinical trial in the primary health care setting. The intervention will be evaluated by external review of the records of deceased patients at 18 months after study onset (Fig. 1).

**Fig. 1 Fig1:**
[figure not shown]
Study design

### Randomization

Each of the 30 participating primary health care centers will be randomly assigned to the intervention or control group. Randomization and concealment will be centralized, through a single coordinating center, using a computer-generated block randomization in blocks of six.

### Setting

IB Salut is a public health organization in the Spanish National Health System, in which universal tax-funded health care services are provided to every citizen, and services are free at the point of access. Each patient is registered with one primary health care center. The Balearic Health Care Service covers the entire population of the Balearic Islands. Majorca is the largest island (850,000 inhabitants), and has four health districts (North, South, East and West Health Districts), each of which has a general hospital and several primary health care centers. PC services in Mallorca Island are provided by 3 PC units in non-acute hospitals and a PC home-based service, with 7 teams of physicians, nurses, and psychologists.

Primary health care centers from 3 health districts in Majorca will participate in the study. The intervention will be managed in the North Health District, which has 6 primary health care centers.

The intervention will be evaluated in 2 health districts: the South Health District (264,757 inhabitants), which has a university hospital and 14 primary health care centers, and the East Health District (326,988 inhabitants), which has a general hospital and 16 primary health care centers.

### Inclusion and exclusion criteria

Inclusion criteria: Primary health care centers from 2 health districts in Majorca.

Exclusion criteria: Unwillingness to participate.

### Intervention

The intervention consists of:

#### Appointment of palliative care leaders (nurses or doctors)

The leader will attend a 42 h training course in PC that is based on the “White Book” of PC training [29]. The role of the leader is to train and promote PC, and to act as a consultant and liaison between the PC home-based services and professionals in the primary health care services.

There will be regular contact with the leaders to monitor the implementation of the proposed activities, and to motivate and promote commitment towards the project. At the same time, leaders will be empowered by emphasizing the value of their roles at each meeting, their importance as “agents of change”, and the need for their commitment to assure the project’s success. Moreover, there will be biannual meetings, convened by the managing center of the Palliative Care Program of the Balearic Islands. The leaders in primary care, the PC home-care team, and the management of the primary health care team will attend these meetings. These meetings will review and discuss the leaders’ functions, assess and elaborate upon support documents, and identify the leaders’ training needs. A virtual shared space will be created using SharePoint (Microsoft) on the IB Salut corporate intranet to enable sharing of support documents, consultation papers, and all new information of interest to the leaders.

#### Identification of patients needing palliative care and classification according to case complexity

Leaders in the early identification and assessment of case complexity of patients receiving referral to PC home-based services will train primary health care doctors. Professionals will use two tools in the electronic clinical record: NECPAL CCOMS-ICO© [7] and e IDC-PAL [30].

The NECPAL CCOMS-ICO© questionnaire was developed by the QUALY/CCOMS - ICO Observatory. It is based on the GSF-PIG [31] and SPICT [32], and adapted for the Spanish language. This questionnaire identifies patients in need of palliative measures, especially non-specific PC services (primary health care and general hospitalization). It is a screening tool (not a prognostic tool) for the early identification of patients needing PC. When a patient needing PC is identified, he/she is classified according to the complexity of the case to determine the most suitable, effective, and efficient care. IDC-PAL is a tool for determining the complexity of PC that is needed for patients with advanced-stage or terminal diseases [30]. This questionnaire considers situations and items that are identified after assessment of the patient-family unit by a multi-professional team. Based on the results of both questionnaires, patients will be classified as not eligible for PC, eligible for simple PC, or eligible for complex or highly complex PC (Fig. 2).

**Fig. 2 Fig2:**
[figure not shown]
Identification and classification of patients needing palliative care

We have already developed training materials on the early identification of patients needing PC, and this includes a video about case complexity and the classification tools (IDC-PAL and NEC-PAL) and PowerPoint presentations to help explain the roles of primary health care leaders, GPs and nurses in PC.

#### Evaluation and integral management of needs

Professionals in primary health care teams have always cared for patients needing PC. We intend to give these professionals more skills and support resources, such as updated information, reference leaders in home-based PC services, diagnostic tools, and regular meetings for discussion of clinical cases with PC experts. Our main objective is to improve the care of non-hospitalized patients who require PC.

### Outcome measures

#### Primary outcomes

Early identification (90 days before death), by GPs and nurses, of patients who are least 18 years-old and need PC based on electronic records.

#### Secondary outcomes

Evaluation of case complexity among patients needing PC, based on electronic records.Patients who die at home.Total number of hospital admissions during the final month of life.Total number of emergency room admissions during the final month of life.Percentage of patients with any of the following “determinants of aggressive end-of-life care” during the final month of life [33]:1 or more admission to the emergency room.1 or more admission to the hospital.1 or more admission to the intensive care units (ICU).More than 14 days in the hospital
Cost of resources during the final month of life includes emergency department visits, outpatient office visits, primary health care visits, inpatient hospital stays, and ICU admissions. Total costs will be calculated by standard cost-per-unit prices, obtained from the Balearic official regional bulletin (17).

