### Data collection

Early identification of patients, resource utilization, and place of death will be estimated relative to the number of patients who could benefit from PC services (causes of death: ICD codes C00-C97; 100–152, 160–169, N17, N18, N28, 112, 113, K70-K77, J06-J18, J20-J22, J40-J47, J96, G10, G20, G35; G122, G903, G231.F01, F03, G30, R54, B20-B24), using the calculation of the potential population size for PC developed by Rosenwax [8, 9]. The causes of death will be identified by review of the death certificates of patients who died 9 to 21 months after the onset of PC.

The NECPAL and IDC-PAL are integrated in the electronic records of GPs, thereby allowing early identification of patients needing PC and evaluation of case complexity. We will extract data from the electronic records upon completion of the NECPAL to identify the need for PC, estimate case complexity using IDC-PAL, and record all emergency department visits, outpatient office visits, primary care visits, duration of all hospital stays, and ICU admissions.

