## Discussion

Our objective of establishing PC leaders is to improve the PC provided by general and specific services. A more comprehensive and community-oriented approach to PC will provide better results if multiple health care professionals work together at the end of a patient’s life.

The role of primary health care is important for early identification of patients eligible for PC. The major aim of the proposed intervention is to increase the early identification of patients through the appointment of a specially trained PC leader (primary health care doctor or nurse) to each team. Thus, we expect that this intervention will sensitize doctors and nurses in the primary health care team so they can identify patients earlier using NECPAL, assess case complexity using IDC-PAL, and then provide essential care to patients requiring simple PC or more complex PC (home-based PC teams, or PC units in the hospital) when patient needs exceed their abilities, thereby avoiding hospitals admissions when possible.

The intervention efficacy will be measured as the increased early detection of patients needing PC, and by improvements in care and use of resources. To determine the effectiveness of the intervention, we will use secondary data from patients’ clinical records (administrative data), in each cases whose underlying cause of death was consistent with receipt of PC.

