Previous studies have used secondary data from clinical records to assess health cost reductions in PC programs [35, 36] and to detect determinants of aggressive end-of-life care [33]. Aggressive or excessive care at the end-of-life can modify the course of disease, but at the expense of good management of symptoms and establishment of an advanced care plan [37]. We are aware of the limitations of assessing the quality of PC based on “service use” and “care management”, rather than factors more directly related to the patient’s and family’s biological, social, and psychological experiences [38]. Many studies have examined the use of aggressive care at the end of life [33, 39, 40]. There is general agreement that a patient spending many hours of the last month of life in an acute care bed or repeatedly accessing acute care emergency services are indicators of poor care at the end of life [37, 38, 41]. Information in patients’ electronic records and variables taken from deceased patients’ records have great value for research and training. Electronic health care records enable researchers to follow patients more easily [42], and to assess the efficacy of programs that seek to change the management system. The strategy of measuring the effect of an intervention via database review is not yet common in RCTs, but it avoids the recruitment problem, the response shift, ethical problems, and selection bias [43]. We will analyze all randomized centers, even if they do not consolidate the role of PC leader or implement the proposed intervention, in our intention to treat analysis.

Another limitation of this study is the method used to determine which patients should receive PC [9, 24]. It is not possible to identify all patients who have a condition making them potentially eligible for PC. We estimated that approximately 75% of patients who die due to cancer, organ failure, and dementia/fragility could be helped by early identification for PC. Moreover, because we cannot identify all potentially eligible patients, if our proposed intervention shows efficacy under the conditions of this study, this indicates that its actual effect could be even greater.

If our results show a positive effect of the intervention, this approach could be replicated in other countries where primary health care is organized into teams, and the GP acts as the gatekeeper.

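### The aggressive-care composite does not separate acute beds from palliative care unit beds, so read literally a palliative care unit stay scores as aggressive care

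*Protocol article*

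**What the plan says.** All references are to the protocol article.

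- **Secondary outcomes** lists a composite, the percentage of patients with any of several "determinants of aggressive end-of-life care" in the final month of life. Two of its components are "1 or more admission to the hospital" and "More than 14 days in the hospital". The others concern the emergency room and intensive care. A separate outcome is "Total number of hospital admissions during the final month of life". None of the hospital items is limited to a type of hospital, ward or bed.
- **Data collection** says that the extraction will cover "duration of all hospital stays, and ICU admissions", again without a distinction by bed type.
- **Setting** states that "PC services in Mallorca Island are provided by 3 PC units in non-acute hospitals and a PC home-based service".
- **Discussion** says that primary care teams should provide essential care themselves or turn to "more complex PC (home-based PC teams, or PC units in the hospital) when patient needs exceed their abilities". Later it supports the indicator by saying that poor end-of-life care is shown by "a patient spending many hours of the last month of life in an acute care bed", or by repeated use of acute emergency services.

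**The concern.** The stated rationale concerns acute care, while the written rule concerns hospital care of any kind. Palliative care unit beds fall between the two: outside the rationale, because they are in non-acute hospitals, but inside the literal wording of the admission and 14-day components. They are also part of the care model under test, since the abstract's background lists hospital palliative care units as one of its three elements.

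At stake is how the composite is read. A patient moved from an acute ward to a palliative care unit has received what the programme offers for complex needs, but on these two components may look no different from a patient who stayed on the acute ward. If unit use differs between arms, the composite mixes a change in acute care with a change in palliative care, and its label would describe both as aggressive care.

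**Working it through.** The plan gives no figure for this point, so there is none to reproduce. The check has two parts.

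**1. Scoring example patients.** Days are those in the final month. The 14-day item is read as cumulative, which the wording allows. None of these patients has an emergency or intensive care contact.

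| Patient | Literal rule: admission / >14 days | Acute beds only: admission / >14 days |
|---|---|---|
| A: 15 days on an acute ward | yes / yes | yes / yes |
| B: admitted from home to a palliative care unit for 15 days | yes / yes | no / no |
| C: 10 acute days, then 5 unit days (10 + 5 = 15) | yes / yes | yes / no |

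The literal rule cannot tell A, B and C apart. With an acute-only rule, B becomes negative on the composite. C stays positive through the acute admission and changes only on the 14-day component. So the composite is affected only through patients like B, who have a unit stay and no other qualifying event. The abstract gives different cut-offs for these indicators. That is a separate matter, because neither set distinguishes bed types.

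**2. What this could do to a comparison.** For the admission component in each arm:

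all-stay risk = acute-admission risk + unit-only admission risk

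Every rate below is assumed; none is in the document. Take acute admission as 50% in control and 45% in intervention (a true difference of -5 points), and unit-only admission as 5% in control and 5% + x in intervention. The all-stay risk in control is 50 + 5 = 55%.

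| x (points) | All-stay, intervention | All-stay difference | Acute-only difference |
|---|---|---|---|
| -2 | 45 + 3 = 48% | -7 | -5 |
| 0 | 45 + 5 = 50% | -5 | -5 |
| +2 | 45 + 7 = 52% | -3 | -5 |
| +5 | 45 + 10 = 55% | 0 | -5 |
| +8 | 45 + 13 = 58% | +3 | -5 |

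Starting from 60% and 55% gives the same differences, because the distortion is simply x.

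With equal unit use (x = 0) the absolute difference is kept and the ratio is diluted: 45/50 = 0.90 becomes 50/55 = 0.91. With higher unit use in the intervention arm the comparison moves against the intervention; with lower use it moves in its favour.

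A second assumed scenario gives a smaller scale. If the intervention added unit stays in 1% to 5% of decedents, and half of these had no other qualifying event, the composite would rise by 0.01 × 0.5 = 0.5 points to 0.05 × 0.5 = 2.5 points. These figures show how the mechanism works; they do not estimate its size.

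**The case against.** The strongest case on the other side has four parts.

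- **The protocol never says in words that unit stays count.** The indicator comes from a cited source that is not at hand, and a condensed article may leave the meaning of hospital to a fuller document. Extracting all stays is not the same as scoring all stays, and it is what would make later classification possible. This stands as a limit: the finding is about the literal reading. It does not remove the point, because the outcome is worded without restriction and the same article gives a narrower rationale.
- **The intervention is aimed mainly at home care.** The abstract and the Intervention section describe referral to home-based teams. The Discussion names home-based teams before units, and the same sentence ends with the aim of keeping patients out of hospital where that can be done. This stands. Units are one stated destination, not the main one, and fewer admissions is itself a legitimate goal.
- **Bias against the intervention is not shown.** A reader might infer from the pathway that the comparison must be biased against the intervention. The documents do not support that. The units serve the island and are open to patients in both arms, no passage gives or predicts a net rise in unit use in the intervention arm, and better home support could lower it.
- **Admissions also measure service use.** Limiting the total count to acute beds would drop a real resource from it and could hide a shift between settings. This stands and shapes the fix.

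**Conclusion.** The point holds in a limited form. As worded, the admission and 14-day components of the aggressive-care composite take in stays in palliative care units, although the article's own rationale is about acute beds and it lists those units as one destination for complex cases. The composite is blurred in both arms, and would be biased against the intervention only on the condition that the intervention raises unit use.

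The size cannot be determined: the document gives neither the share of deaths with a unit stay nor the difference expected between arms, and all percentages in the working are assumptions.

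A reader might also infer that the trial could not show any improvement in end-of-life care. That goes too far. Death at home, the emergency outcomes and the intensive care component do not depend on bed type and could still show a change. The primary outcome, early identification, is untouched.

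**What to change.** In Secondary outcomes:

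- Define the hospital-admission and more-than-14-days components of the composite on acute-care hospital beds, identified by hospital or ward type in the records already to be extracted.
- Keep total admissions and costs on all stays, as measures of service use, but split them into acute and palliative care unit.
- Report palliative care unit admissions and days separately by arm, so that a shift between settings can be seen.

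The cost is a change of outcome wording and a hospital or ward-type field in a planned extraction, with no extra patients. The article does not say whether that field is held, so this should be confirmed. Two small downsides remain: stays with a transfer must be divided into acute and unit days, and the composite becomes less directly comparable with any source that counts all stays.
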